#### Training and support

Prior to commencing the FRNs will be provided with a one day training program on falls prevention, action research, practice change and other aspects of the project, such as data collection processes. A test of knowledge of falls risk factors and prevention interventions will be completed by FRNs at the beginning of the training session. One week after the training program, FRNs will be emailed the test and asked to fill it in and return it without referring to any written materials and allowing approximately an hour to complete.

In addition to the training program, FRNs will be provided with a resource pack which will incorporate key information from international best practice guidelines such as the RNAO guidelines (Canada) [28] and the NICE guidelines (UK) [29] as well as the Victorian Quality Council falls prevention guidelines [23], the Australian Safety and Quality Council's guidelines [30]. FRNs and FARG members will also have access to expert advice from the multidisciplinary research team including physiotherapists, nurses, social workers and a geriatrician. The FARG will also have an initial training session with a nurse experienced in undertaking action research in these settings. Project officers will also have regular teleconferences with this nurse to discuss action research processes and discuss any problems arising.

Facility wide interactive falls prevention training will be run at each facility. Development and implementation of the program will be tailored to the specific needs of each facility and may be part of the action plan developed in the FARGs. The training will aim to spread the message that falls prevention is everyone's responsibility.

#### Falls risk assessment

The Falls Risk for Older People - Residential Care (FROP-RC) will be completed for all consenting residents [31]. This tool will be modified slightly from a previously validated falls risk assessment tool for the sub-acute hospital setting [32]. The tool will either be completed by the FRNs, other FARG members and/or with an external allied health professional depending on the capacity of each facility to conduct the assessments as well as the decisions of the FARGs. The individual resident falls risk assessments will be used to inform individualised strategies. The assessments will also identify falls risk issues that are able to be addressed facility wide. Data will be entered into an excel spreadsheet for analysis. The research team will provide facilities with trend data, e.g. a high proportion of residents having a particular modifiable risk factor.

#### Equipment and modifications

The project budget allows a set allocation of funding for each facility to spend on environmental modifications, hip protectors for residents with high risk of repeated falls/injury and one or two hi-lo or lo-lo beds. The use of these funds is at the discretion of FARGs and managers in each facility, with approval from the external project manager. The environmental audit undertaken in the scoping phase will include a list of areas that could be improved in each facility. Facility staff will use this list to determine which modifications they think will be most useful in preventing falls in their facility.

#### Economic evaluation

A cost effectiveness analysis will be conducted as a part of this project from societal and health-service provider (residential aged care facility) perspectives. The costs of program implementation will be tracked during project implementation and valued at market rates where available. Costs averted from the prevention of falls and fall-related injury will be calculated by comparing fall and fall-injury rates before and after intervention commencement with modelling of cost-per fall data captured from two of the participating sites. This cost-per falls data will include costs of hospitalisation to treat fall-related injuries, costs of transportation to hospitals, and costs of visits by and to general practitioners/other health professionals to treat fall-related injuries.

#### Steering committees

Within each facility an organisation based steering committee will be established. There are two instances where two facilities are part of one organisation and are indicating a preference for a joint steering committee to be formed, resulting in a total of seven committees. The purpose of each committee is for the research team to consult with key players within the organisation throughout the duration of the project and to keep them informed of project progress and outcomes. Key responsibilities of the committee will include: overseeing the project at an organisation level; monitoring research activities and providing feedback regarding research findings; being a resource to the research team and providing advice from an organisation specific perspective; and discussing strategies for maximising sustainability after project completion.

#### Evaluation

Falls incident data will be reviewed by the project team on a six monthly basis throughout the project and will be reported back to facilities at six and 18 months. As previously described, each FARG will also develop and complete site-specific evaluations relevant to the action plan implemented. After completion of the FARGs, the sustainability model questionnaire, the falls scoping survey and the safety culture survey will also be readministered to gauge any other changes during the project.

Final resources for dissemination of project processes and outcomes will be developed and disseminated. Findings will be collated into facility specific reports for facilities to review outcomes as well as an overall final evaluation report combining data from all sites and incorporating the economic evaluation.

### Analysis

Data from the questionnaires and surveys will be analysed using the appropriate non-parametric statistical analyses. Responses to individual items of the survey of safety culture will be compared between groups using ordinal logistic regression analysis, clustering results by the site from which the data was collected.

The rate of falls per resident observed year will be compared between pre intervention and during intervention period using a generalised estimating equation [33]. The monthly number of falls at each facility is the individual unit of measurement. Monthly data by facility will be coded by whether it is collected during the pre-intervention or intervention period. Intervention period data will be additionally coded by whether the data is collected during an "active" intervention period or during an "inactive" intervention period (after completion of the FARGs). Generalised Estimating Equations will be conducted using a Poisson outcome measure distribution family and an exchangeable working correlation structure, though the correlation structure will be checked prior to analysis to determine if the exchangeable structure is still the most appropriate. Adjustment will be made for the number of resident observed years at each site per month. Pre/during intervention and active/inactive intervention variables will be entered into this model as explanatory variables.

For the economic evaluation, the change in costs allocated for the prevention of falls and treatment of fall-related injuries between the pre-intervention and during intervention periods will be the numerator. The change in the number of falls per month (adjusted for resident observed years) will be the denominator, culminating in a cost per fall prevented ratio. Several cost-effectiveness models will be developed by modelling an extended time-line of the project duration for +1, +2, +3, +4 and +5 years beyond the cessation of the implementation phase. The difference between active and inactive period fall rates will be used to guide this modelling. Further sensitivity analyses will be conducted by modelling clinically reasonable variations in the key outcome (falls) and cost (e.g. staffing) measures collected.

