### Recruitment of facilities and participants

RACFs were approached in three states across Australia, and all accepted the invitation to participate in the project. These facilities were selected purposively to represent a range of sizes, target groups, and geographic features, including high and low level care, dementia specific, rural/regional, metropolitan, ethnic specific or psychogeriatric. All except one facility are not for profit organisations and some are linked to health services. Across the nine participating facilities approximately 670 people reside and 650 staff are employed. All staff and residents will be invited to take part in at least one component of the project.

Each facility is allocated funding to release a nurse staff member to the role of key contact and project support person known as the falls resource nurse (FRN, 0.1 EFT) for the project. The secondment provides an opportunity for the staff member to undertake project activities without being distracted from their existing workload. It is anticipated that this process would contribute to ongoing sustainability through building capacity within the facility. An additional 0.1 EFT funding is provided to support other areas of staff time and engagement in specific falls prevention activities.

With the assistance and advice of the FRN in each of the facilities, residents and families will be informed of the research. Methods of informing and engaging residents and families will include attendance at family meetings, flyers distributed on family and resident notice boards and distribution of project information through facility mail outs.

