A safety culture survey for residential aged care facilities will be used to assess safety culture and hazard reporting at baseline to inform action research. This survey has been adapted from the safety culture survey for hospitals [25]. The survey will be researcher administered to all facility staff working within a 24 hour period, including staff working on night, day and evening shifts.

To measure how each facility will sustain project activities, the sustainability model questionnaire will be completed with the action research groups [26].

At the completion of the scoping phase, an individualised report will be provided to each facility, highlighting areas being well implemented, and areas where additional activity needs to be targeted. This will form the basis for the Action Research Groups to identify gaps in evidence based practice to address in the implementation phase within each facility.

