### Ethics

This project was approved by local human research ethics committees for each site (Ballarat Health Service & St John of God Human Research Ethics Committee; Toowoomba & Darling Downs Health Service District Human Research Ethics Committee; Human Research Ethics Committee St Vincent's Hospital; Tasmania Social Sciences Human Research Ethics Committee).

All staff in each facility will be provided with a Plain Language Statement and Consent Form inviting their participation in the study (for example, training, focus groups, FARGs, surveys, reviews of various documents and tools).

Managers and/or FRNs will identify residents who will be able to give informed consent and provide them with a Plain Language Statement and Consent Form to obtain consent for various components of the project that are outside usual care, such as audits to their rooms, additional falls risk assessment, or implementation of safety devices such as hip protectors. For those residents unable to provide informed consent due to cognitive impairment, facility staff will provide relatives/contact persons with a Plain Language Statement and Consent Form to seek consent for participation on behalf of their family member residing in the participating facility.

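### The safety culture model uses site only for clustering, so a change in the site mix of respondents that is related to culture would bias the follow-up v baseline odds ratio

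*Protocol article*

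**What the plan says.** The Analysis section of the protocol article gives the method for individual safety culture items in one sentence: they will be "compared between groups using ordinal logistic regression analysis, clustering results by the site from which the data was collected". It names no site covariate, stratum or random effect, and does not say what the groups are.

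The sampling is described elsewhere in the article:

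- Baseline scoping: "The survey will be researcher administered to all facility staff working within a 24 hour period". No number per site is fixed, and no linking of individuals across waves is described.
- Evaluation: after the action research groups finish, "the safety culture survey will also be readministered to gauge any other changes during the project". The compared groups are therefore, by inference, the two survey waves.
- Ethics: "All staff in each facility will be provided with a Plain Language Statement and Consent Form inviting their participation in the study". Surveys are among the listed activities, so answering is voluntary.
- Recruitment of facilities and participants: "These facilities were selected purposively to represent a range of sizes, target groups, and geographic features", and "Across the nine participating facilities approximately 670 people reside and 650 staff are employed".

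For the falls model, by contrast, the same Analysis section names the period terms ("Pre/during intervention and active/inactive intervention variables will be entered into this model as explanatory variables"), the exposure adjustment and the working correlation.

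**The concern.** Clustering by site normally means cluster-robust standard errors. These correct the uncertainty for similarity among staff of one facility, and leave the point estimate as it would be if site were ignored. That estimate compares all follow-up respondents with all baseline respondents.

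The survey is a repeated cross-section, so the two sets of respondents need not be spread over the nine sites in the same proportions. If sites with a better safety culture supply a larger share of the follow-up answers, the pooled odds ratio rises even though no site has changed. If they supply a smaller share, a real improvement is partly hidden. At stake is whether a reported change in culture can be read as change within facilities. Site is recorded, since the plan clusters on it, so this alternative explanation can be removed.

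**Working it through.** The plan states no figure for this comparison, so there is none to reproduce. The check asks how far the pooled odds ratio moves when the true within-site odds ratio is 1.00.

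**Inputs from the documents.** Nine sites; about 650 staff, or 650/9 ≈ 72 per site on average; two waves; site used for clustering only.

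**Inputs that are assumptions.** About 22 to 25 respondents per site and wave (22 × 9 × 2 = 396, roughly 400 in all); a five-level item; the between-site SD on the log-odds scale; and the size and direction of the change in mix.

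**Step 1: approximation.** Let site *s* have log-odds effect *u_s*, a baseline share of 1/9 and a follow-up share of (1 + *d_s*)/9, with the *d_s* averaging zero. With no within-site change,

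log OR ≈ Σ (follow-up share − baseline share) × *u_s* = (1/9) Σ *d_s u_s* = (8/9) × ρ × CV × SD,

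where ρ is the correlation of *d_s* with *u_s*, CV is the SD of *d_s*, and SD is that of *u_s*. The shift is zero if the mix does not change (CV = 0), if the sites do not differ (SD = 0), or if the two are unrelated (ρ = 0).

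**Step 2: a 30% change in mix, correlated 0.7 with culture.**

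- SD 0.5: (8/9) × 0.7 × 0.3 × 0.5 = 0.093, and exp(0.093) = 1.10.
- SD 1.0: (8/9) × 0.7 × 0.3 × 1.0 = 0.187, and exp(0.187) = 1.21.

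Two separate simulations of this setting, with cumulative logit models fitted to each data set, gave mean odds ratios of 1.10 to 1.14 and of 1.08 to 1.19 without site terms. With site indicators they gave 0.99 to 1.00 and 0.99 to 1.01.

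**Step 3: sensitivity to the assumptions.** Here the four higher-scoring sites gain, and the four lower-scoring sites lose, a fixed percentage of respondents at follow-up. The proportional-odds model was fitted to expected counts with 25 per site at baseline.

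| Site SD | No change | 20% | 40% | 60% |
|---|---|---|---|---|
| 0.3 | 1.00 | 1.05 | 1.10 | 1.15 |
| 0.5 | 1.00 | 1.08 | 1.16 | 1.25 |
| 0.8 | 1.00 | 1.12 | 1.26 | 1.41 |

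These are odds ratios without a site term. With site in the model the result is 1.00 in every cell.

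**Step 4: change in mix unrelated to culture.** The mean estimate is unbiased with or without site terms. Precision results are mixed. One set of simulations gave an SD of the log odds ratio of 0.181 without site terms and 0.170 with them; another gave 0.180 to 0.186 without and 0.187 to 0.191 with. A linear approximation with larger random changes in both waves (log-SD 0.4 in site counts) favoured site terms. No general gain in precision can be claimed.

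**Step 5: error rate.** In that linear approximation (600 replicates, cluster-robust errors, nominal 5%), false positives were about 10% without a site term and 8% with one under random changes in mix. With a constant mix they were 7 to 8% in both. Most of the excess therefore comes from having only nine clusters, and a site term does not cure that.

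**The case against.** The strongest reply is that the sentence does not mention standard errors. Clustering results by site could loosely mean a random site intercept, which would remove most of the bias, and a journal article may leave a covariate list to a fuller plan. This stands as a limit: the standard-error-only reading is the plain one, not a certain one. It does not dispose of the point, because the article does state how site is handled and that handling does not make the comparison within-site.

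A second reply is that the documents limit the driver. The survey is administered by researchers to all staff on duty across all shifts at the same nine sites, so site shares depend largely on rosters and facility size. This also stands. A reader might infer that engaged sites are likely to answer better after a year of project work, so that the planned analysis will show a spurious improvement. Nothing in the documents says that response will change by site, or that any change will follow safety culture. Voluntary consent makes it possible, no more.

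Third, calling the two waves groups is ordinary usage, and the comparison can be recovered from the Evaluation section. That is right: the wording needs clarifying but is not an error in itself.

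Finally, the survey informs the action research and gauges other changes. It enters neither the falls model, the power analysis nor the economic evaluation. That limits the consequence.

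**Conclusion.** The point holds as a conditional bias in a secondary process measure. On the plain reading of the Analysis section, the wave odds ratio pools all respondents, and it is biased if site shares change between waves in a way related to safety culture. Both conditions are needed: sites that differ, which purposive selection makes plausible, and a culture-related change in mix, which is possible but undocumented.

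The size is unknown. Under the assumptions of Step 2 a null effect appears as about 1.1 to 1.2. The wider directed scenarios run from 1.05 to 1.41, and the top of that range needs every higher-scoring site to gain 60% and every lower-scoring site to lose 60%.

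Two stronger readings are not supported: that the result will be biased, and that site terms would reliably sharpen it. The falls analysis is not affected. The change is still worth making, because it is cheap and removes an avoidable explanation for any reported change in culture.

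**What to change.** In the Analysis section, state that the groups compared are the baseline and follow-up survey waves, and that each ordinal logistic model includes wave and site, with site as a fixed effect (eight indicators for nine facilities). The wave odds ratio is then a within-site comparison.

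Clustering by site may be kept, with a note that nine clusters make cluster-robust standard errors somewhat too small. If a random site intercept was what the sentence meant, saying so would resolve most of the concern.

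The cost is a sentence in the plan and no new data. Eight extra parameters on roughly 400 responses (assumed) cost at most a trivial loss of precision. Site terms remove only shifts between sites; a change in which staff answer within a site would remain.

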**Methods:**

The project will be conducted from November 2007-November 2009. The project will involve baseline scoping of existing falls rates and falls prevention activities in each facility, an action research process, interactive falls prevention training, individual falls risk assessments, provision of equipment and modifications, organisation based steering committees, and an economic evaluation. In each RACF, staff will be invited to join an action research group that will lead the process of developing and implementing interventions designed to facilitate an evidence based approach to falls management in their facility. In all RACFs a pre/post design will be adopted with a range of standardised measures utilised to determine the impact of the interventions.

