### Procedure

#### Baseline scoping

To gauge how well facilities are currently implementing evidence based practice, a comprehensive scoping audit will be undertaken at the beginning of the study. This will include: falls incident data, an audit of the current falls prevention activities, environmental audits, a survey on resident safety culture within the organisation and a questionnaire on sustainability.

From each facility, falls data for the six months preceding project commencement will be analysed, including data on circumstances, precipitating factors, consequences and management. These will be reported as falls/1000 resident bed days. Frequency analyses will be used to determine the most common locations, circumstances and consequences of falls.

The falls scoping audit was developed using key falls prevention strategies identified in the Victorian Quality Council's falls prevention guidelines [23] and covers issues such as falls risk assessment, collection and use of falls prevention data, and access to allied health staff. Key interventions covered in the audit include: group exercise, individual exercise, walking aids, hip protectors, medication review, vitamin D and calcium supplementation, toileting assistance program, adequate condition and use of aids for sensory loss, feet in good condition and appropriate footwear, surveillance, hi-lo or lo-lo beds and referral to other health professionals. The Project Officer will send the survey to the FRN to complete. After the FRN completes the survey, the Project Officer will go through it with the FRN to make sure everything is completed and that the Project Officer has full knowledge of the falls prevention activities taking place in the facility.

To identify environmental hazards that may require modification, environmental audits will be completed in each facility. This will involve an audit of resident rooms, indoor and outdoor communal areas of each facility using an environmental audit tool adapted from a tool developed to improve the environment for older people in health services [24]. Recommendations from the environmental audits will be made to participating facilities, and used to assist in the allocation of funds available for environmental modifications as part of the project.

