#### Action research

An action research approach will be used in the facilities as a key element to work towards achieving the project aims. In each RACF staff interested in falls prevention will be invited to join a falls action research group (FARG). To recruit staff, meetings will be held in each RACF to identify volunteers. Eligibility for FARG membership will include any staff member working within the facility (for example, nurse, personal carer, lifestyle, allied health, kitchen, laundry, cleaning staff, management). In some instances it might be relevant to include staff who may not work in the facility but visit on a clinical basis such as a physiotherapist. Five-six staff members will be recruited in each FARG. A project officer will facilitate meetings that will be audio taped and transcribed. The project officer will conduct a first level analysis that will be distributed to the respective FARG members prior to the next meeting to ensure the discussion has been recorded accurately and key points included.

From May 2008 FARG members will meet fortnightly for 12 months to identify key issues, facilitators and barriers to successful falls prevention within their RACF. During these discussions the members will articulate their position on the issues that impact on the occurrence of falls in their facility. Each FARG will draw on findings together with the audit data to determine site specific activities on which to focus their interventions to improve falls prevention in the RACFs.

These activities will be developed into action plans that the FARGs will then implement with support and advice from the project officer. Methods for evaluating these actions will be established and monitored by the FARGs. Project officers will assist in writing up action plans incorporating evaluation measures.

The project officers facilitating the FARGs in each RACF will also maintain a qualitative record of the group's activities or project diary that will provide useful data for determining factors that enabled or prevented the success of the falls interventions. This will be supplemented with thematic analysis of transcripts using NVivo software.

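### The falls model has no calendar-time term, so season is confounded, in unknown direction and size, with change after the action research groups end, and this contrast guides the five-year cost models

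*Protocol article*

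**What the plan says.** The Analysis section of the protocol article sets out the falls model in some detail. On the data: "The monthly number of falls at each facility is the individual unit of measurement". On covariates: "Pre/during intervention and active/inactive intervention variables will be entered into this model as explanatory variables". On exposure: "Adjustment will be made for the number of resident observed years at each site per month". The family is Poisson and the working correlation exchangeable, subject to a check. No month, season or trend term is listed.

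The periods follow from three places:

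- Action research section: "From May 2008 FARG members will meet fortnightly for 12 months".
- Analysis section: inactive data come from the "intervention period (after completion of the FARGs").
- Abstract, Methods: "The project will be conducted from November 2007-November 2009".

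For the baseline, the Baseline scoping section says: "From each facility, falls data for the six months preceding project commencement will be analysed". The article does not say whether November 2007 to April 2008, before the groups start, also counts as pre-intervention.

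The Analysis section then extends the cost-effectiveness models to +1, +2, +3, +4 and +5 years, and adds: "The difference between active and inactive period fall rates will be used to guide this modelling". Sensitivity analyses are to vary falls and costs within clinically reasonable limits. Season is not named.

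**The concern.** A full year is compared with part of a year, in a pre/post design without control facilities and with a model that does not use calendar time. If falls vary by season, the active-inactive contrast mixes that variation with whatever really happens once the groups stop meeting, and the two cannot be separated in the planned model.

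This contrast is the plan's evidence on whether benefit persists, and it informs projections of up to five years. The Discussion intends the economic results to persuade other facilities to invest. A seasonal artefact could make the programme look as if it fades, or as if it keeps improving.

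**Working it through.** **The plan's own figure.** The article gives no figure for the active-inactive contrast. Its 85% power refers to the reduction of 0.7 falls per resident year. It is reproduced by a paired normal approximation with nine facilities, SD 0.7 for the within-facility difference and an assumed two-sided 5% level: Φ(0.7/(0.7/√9) − 1.96) = Φ(1.04) = 0.851. It does not bear on this point.

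**Months in each period, from the stated dates.**

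| Period | Span | Calendar months covered |
|---|---|---|
| Pre, short reading | about May–Oct 2007 | 6; no Nov–Apr |
| Pre, long reading | May 2007–Apr 2008 | all 12 |
| Active | about May 2008–Apr 2009 | all 12 |
| Inactive (inferred) | about May–Oct or May–Nov 2009 | 6 or 7; no Dec–Apr |

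**Seasonal bias with no true change after the groups end.** Assume a monthly rate factor 1 + a·cos(2π(m − p)/12), with amplitude a and peak month p. Both are assumptions. Over a full year the factor averages 1, so the spurious inactive/active ratio is its average over the inactive months. For a July peak the cosines for May to October are 0.5, 0.866, 1, 0.866, 0.5 and 0, with sum 3.732 and mean 0.622. November adds −0.5, giving 3.232/7 = 0.462. A January peak reverses the signs.

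| Amplitude | July peak, May–Oct | July peak, May–Nov | January peak, May–Oct | January peak, May–Nov |
|---|---|---|---|---|
| 5% | 1.031 | 1.023 | 0.969 | 0.977 |
| 10% | 1.062 | 1.046 | 0.938 | 0.954 |
| 20% | 1.124 | 1.092 | 0.876 | 0.908 |

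With no seasonality every entry is 1.

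**Scale against the planned effect.** Suppose the planned reduction (2.6 to 1.9) were fully kept. At 10% amplitude with a July peak, the inactive rate would read 1.9 × 1.046 = 1.99 or 1.9 × 1.062 = 2.02, an apparent loss of 13% to 17% of the 0.7 effect. A January peak would show an apparent further gain of about the same size.

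**Scale against precision.** With 670 residents at 1.9 falls per resident year, the active year yields about 1,273 falls and six inactive months about 637. The Poisson-only SE of the log ratio is √(1/1273 + 1/637) = 0.0485. With seven months (about 743 falls) it is 0.046. At 10% with a July peak the bias is ln 1.062 = 0.060 (1.2 SE) for May–October and ln 1.046 = 0.045 (about 1 SE) for May–November.

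**Active versus pre.** If pre is only May–October 2007, a 10% season alone gives 1/1.062 = 0.94 (July peak) or 1/0.938 = 1.07 (January peak). With May 2007 to April 2008 as baseline the ratio is 1.00.

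**Does a seasonal term remove it?** The planned GEE was simulated with nine facilities, an exposure offset, seven inactive months and 100 runs per setting. At 10% amplitude the mean inactive/active ratio was 1.04–1.05 (July peak) or 0.95 (January peak) without a seasonal term. With an annual sine/cosine pair it was about 1.00 in both cases.

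**Cost in precision.** From the Poisson information matrix with six inactive months:

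| Contrast | Baseline | No term | Sine/cosine | Linear trend |
|---|---|---|---|---|
| Active v pre | 6 months | 0.0440 | 0.0498 (+13%) | 0.1159 (×2.6) |
| Active v pre | 12 months | 0.0369 | 0.0369 (0%) | 0.0719 (×1.9) |
| Inactive v active | 6 months | 0.0485 | 0.0538 (+11%) | – |
| Inactive v active | 12 months | 0.0485 | 0.0512 (+6%) | – |

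**The case against.** The strongest reply has five parts.

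1. **Direction and size are not in the document.** This stands. A reader might infer that season will be mistaken for loss of effect, but that needs falls to run higher from May to November. The article says nothing on this, and the opposite pattern reads as further gain.
2. **The inactive window is inferred, and it is not one season.** This stands. It spans six to seven months, from late autumn through spring, and November 2009 closes the project rather than a stated falls collection. Either end date leaves December to April uncovered.
3. **The bias may be below one SE.** This stands in part. It exceeds one SE with a July peak only for May–October and with Poisson variation alone. As a rough illustration, treat the SD of 0.7 in the Power analysis section as applying to two-month blocks at facilities of about 74 residents. The Poisson SD would be √(2.6/12.4) = 0.46 and the variance ratio about 2.3, which puts a 10% season below one SE in either window. Some of that SD may be between-facility variation. Overdispersion widens the interval but does not remove the bias.
4. **The projection is not mechanical.** A reader might infer that the difference is simply carried forward for five years. The text says it will guide the modelling, and sensitivity analyses vary falls. That softens the consequence, but varying falls around an estimate does not re-centre a biased one.
5. **A condensed article leaves detail to the full plan.** This does not answer the point. The article itself names the explanatory variables and the use of the contrast.

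**Conclusion.** The point holds as a confounding problem of unknown direction and size. It rests on the listed covariates, on a full-year active period set against an inactive period inferred to lack December to April, and on the use of that contrast to guide the +1 to +5 year models. Under an assumed 10% amplitude, the spurious inactive/active ratio is about 1.05–1.06 (July peak) or 0.94–0.95 (January peak), roughly one Poisson-only SE. With no seasonality it is nil. The documents do not support saying that the plan will show a false loss of benefit, or that such a loss will be projected by rule.

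The active versus pre contrast is affected only if the baseline is confined to the six months before November 2007, which the article leaves open. The change is worth making because it is cheap and uses data already planned.

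**What to change.** - Add annual sine and cosine terms to the GEE.
- Take the persistence input and its confidence interval from that season-adjusted model, and carry the interval, not just the point estimate, into the +1 to +5 year models.
- State which months count as pre-intervention. May 2007 to April 2008 would balance active versus pre by season.
- Report the inactive months of 2009 against the same calendar months of 2008 as a sensitivity analysis only. Those 2008 months are the groups' start-up, when they are still identifying issues and drawing up action plans, so the comparison could hide real waning.
- Report a linear-trend model as a sensitivity analysis only, because it multiplies the active versus pre SE by about 2 to 2.6. The sine/cosine pair does not address drift.

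The cost is two extra model terms, an SE increase of about 0 to 13%, and the assumption of one common seasonal shape across nine purposively varied sites in three states.
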